## Abstract

**Background:**

Gastrointestinal cancers represent one of the most prevalent diseases worldwide. Strikingly, the incidence of Early Onset Gastrointestinal Cancer (EOGIC) has been rising during the last decades and changes in lifestyle and environmental exposure seem to play a role. EOGIC has been defined as a different entity compared to on-average gastrointestinal cancer, with distinct clinical and molecular characteristics. Inherent to the particularities of younger age, there is an unmet need for a tailored approach for the management of these patients. The TEOGIC proposes a comprehensive study to characterize EOGIC patients in the northern of Spain.

**Methods:**

Patients with histologically confirmed new diagnosis of colorectal, gastroesophageal and pancreatic adenocarcinoma will be considered for two cohorts: EOGIC (≤ 50 years old) and non-EOGIC (60–75 years old), with a ratio of 1:2. Two hundred and forty patients will be recruited in 4 Public Hospitals from northern Spain. After receiving unified informed consent, demographic and clinical data of the patients will be collected in a REDCap database. Lifestyle related data will be obtained in questionnaires assessing diet, physical activity and the general quality of life of the patients before diagnosis. Biological samples prior to any onco-specific treatment will be obtained for the analyses of circulating inflammatory proteins, gut microbiota, and the proteome of the tumor microenvironment. Histologic characteristics and routine biomarkers will be also collected. Thereafter, data will be integrated and analyzed to assess tumor specific, pan-tumor and sex-associated differential characteristics of EOGIC.

**Discussion:**

The underlying risk factors and differential characteristics of EOGIC remain poorly studied, particularly in our geographical area. Although limited by the exploratory nature and the small sample size estimated to be recruited, TEOGIC represents the first attempt to comprehensively characterize these young patients, and thus attend to their special needs. Findings derived from this study could contribute to raise awareness and preventive behaviors in the population. In parallel, molecular studies could lead to the identification of potential novel non-invasive biomarkers and therapeutic targets that would help in the development of the tailored clinical management of these patients, focusing on screening programs for early diagnosis and precision medicine.

## Background

Gastrointestinal (GI) cancer includes malignant tumors of the GI tract such as colon, rectum, esophagus, stomach, pancreas, liver and biliary tract. In 2020, colorectal was the cancer with the third highest incidence and the second cause of cancer-related deaths worldwide. The global incidence and prevalence of other GI cancers was also relevant that year, in this regard, both gastroesophageal and pancreatic cancer represented 11.7% of all new cancer diagnoses and 17.9% of all cancer-related deaths [1]. In Spain, estimated incidences by 2024 ranked colorectal, pancreatic and gastroesophageal as the first, seventh and ninth most incident cancers, respectively [2]. Even though a global decreasing incidence of colorectal and gastroesophageal cancer is observed, some studies show an increase in Early-Onset GastroIntestinal Cancer (EOGIC), defined as that diagnosed in the population below 50 years old. Considering pancreatic cancer, both on average-onset and early-onset incidences are gradually growing [3–6]. Specific data regarding cancer incidence among young adults are still lacking in our country.

Several studies have assessed the occurence of germline mutations in patients with EOGIC [7, 8], however only a small fraction is linked to a hereditary cancer predisposition syndrome, since most of EOGIC cases are sporadic. Therefore, the increase in EOGIC incidence in the last years seems to be influenced by environmental factors such as changes in diet and lifestyle. Obesity, sedentary habits and some dietary patterns are well-known cancer risk factors and are prevalent among young adults developing GI tumors [5, 9–12]. The increased incidence in developed countries of early onset colorectal cancer (EOCRC) or gastroesophageal cancer (EOGEC) also support the hypothesis of environmental factors playing a role in this trend. In this regard, alterations in the gut microbiota due to antibiotic consumption, eradication of *H. pylori* infections or autoimmune atrophic gastritis have been associated to EOCRC and EOGEC [3, 13–16].

Some studies have assessed differential clinical and molecular characteristics of EOGIC, proposing the recognition of a novel entity with special requirements for diagnosis and clinical management. EOGIC usually presents in advanced clinical stages and with aggressive phenotypes, including poor differentiation, signet ring histology and vascular-perineural invasion [17]. EOCRC typically occurs in the distal colon and rectum, with a higher proportion of microsatellite unstable tumors, fewer cases of mutations in *APC*, *KRAS*, and *BRAF*^V600E^, and mostly with a molecular subtype related to infiltration of inmune cells [18–20]. Interestingly, it has been linked to a distinctive microbiota [21]. EOGEC commonly associates with atrophic gastritis from autoinmune phenomenons. It presents higher tumor grades, higher proportion of poorly cohesive histology and signet-ring cell subtype, with an increment of CDH1 mutations, as well as the molecular subtype EBV (TCGA classification) [20, 22]. Early onset pancreatic cancer has lower proportion of *KRAS*, while *SMAD4* mutations are more frequent. Different signaling pathways like Hedgehod, TGFβ, hypoxia or PI3K/AKT have also been reported in these patients [23, 24].

Additionally, EOGIC patients have distinctive characteristics that affect their clinical management. Due to their extended life expectancy, they face long-term effects from therapeutic strategies, which may impact their quality of life and more specifically their sexual and reproductive health. Furthermore, cancer diagnosis at a young age normally represents a more pronounced psychological disorder derived from its impact on professional, social and familiar commitments. This is why it is essential to treat these patients individually, considering all these factors and providing a more personalized and precise approach [6, 25–30].

In summary, available evidence suggests that environmental factors underlie most of the increased incidence of EOGIC, although with geographical differences [3]. Available studies also suggest that EOGIC represents a distinct entity with differential molecular signatures that affect the tumor physiopathology and patients’ outcomes. Besides, young patients need a distinct approach considering their longer life expectancy and unique familiar and social commitments. In Spain, comprehensive studies focused on the incidence and characterization of this population are still lacking. In a retrospective study analyzing locally advanced rectal cancer recently published by our group, we observed that patients diagnosed at a young age (≤ 50 years old) showed higher rates of response to neoadjuvant therapy compared to older patients, which suggests that these patients could benefit from a tailored clinical management [31].

## TEOGIC study methods

### Study design and aim

TEOGIC is an observational, transversal and multicenter study with the objective of characterizing EOGIC (i.e. diagnosed in patients ≤ 50 years old) in comparison to non EOGIC from a comprehensive approach, covering aspects from tumor biology to patients´ lifestyle.

Project investigators comprise a multidisciplinary team involving Public Hospitals, a Biomedical Research Center, and a research group specialized in oncology data science. The project is led by the Health Research Institute of Navarra (IdiSNA), including the University Hospital of Navarra (HUN)-Pamplona-Iruña and the Biomedical Research Center Navarrabiomed. Three more Hospitals of the Northern area of Spain participate in patient recruitment: Miguel Servet Hospital (HMS)-Zaragoza, University Hospital Donostia (HUD)-San Sebastián-Donostia and San Pedro Hospital (HSP) Logroño. ODysSey, from the Vall d´Hebron Institute of Oncology (VHIO)-Barcelona will be in charge of the management, integration and interpretation of multiomics and clinical data.

### Patient selection and recruitment

Patients will be selected and recruited in routine medical appointments by specialized medical oncologists at the participating Hospitals during the period of 01/2024–12/2025. Patients will be included consecutively based on inclusion and exclusion criteria, following a ratio of 1 EOGIC: 2 non-EOGIC.

#### Inclusion criteria

Patients with newly diagnosed, histologically confirmed colorectal adenocarcinoma (CRC, group A), gastroesophageal adenocarcinoma (GEC, group B) and pancreatic adenocarcinoma (PC, group C).Age 18–50 (both included) years old for the EOGIC group, and 60–75 (both included) years old for the non-EOGIC group.

#### Exclusion criteria

Eastern Cooperative Oncology Group (ECOG) performance status of ≥ 3.Presence of comorbidities which may compromise participation of the patient in the study (mainly in terms of capability to complete the questionnaires).Having received oncological treatment directed at the newly diagnosed cancer (i.e., at the time of inclusion the patient has not yet started any type of treatment, including surgery).

Although there is a lack of consensus in the age threshold to define EOGIC, it is generally set at 50 years old, in agreement with the initiation of most of the screening programs [6]. Regarding the non-EOGIC group, we set the lower age at 60 years old, in order to ensure a clear differentiation between groups; while the upper limit is established at 75 years old in order to exclude the very elderly population. Again, although the lack of consensus in the age to define elderly patients, several studies in the field consider 75 years old as the lower limit to define this population, and present evidence on their differential characteristics compared to on-average patients [32–36]. Age range is also defined with the objective to minimize age related confounding effect.

We estimate the following number of patients to be included in each group: CRC-group A, 40 EOGIC and 80 non-EOGIC; GEC- group B, 20 EOGIC, 40 non-EOGIC; PC-group C, 20 EOGIC, 40 non-EOGIC (Fig. 1a). Estimated number of patients has been calculated based on incidence of EOGIC in HUN in the years 2019–2022 (Fig. 1b), and assuming a similar incidence in the other participating hospitals, taking into account that all participating Hospitals cover a similar target population. The rate of patient inclusion will be evaluated periodically and if necessary, recruitment period will be extended or additional Hospitals of the geographical area will be invited to participate in the study in order to increase patient recruitment.

**Fig. 1 Fig1:**
[figure not shown]
Estimated patient recruitment. **a** Diagram of the recruiting centers and estimated number of patients to be recruited by group. **b** Number of cases with GI cancer treated in Medical Oncology Unit of the HUN in the years 2019–2022. Red depicts EOGIC, while green depicts non-EOGIC (age > 50 years) CRC: colorectal cancer; EOGIC: early onset gastrointestinal cancer. GEC: gastroesophageal cancer; PC: pancreatic cancer

As aforementioned, patients will be included in a ratio of 1 EOGIC: 2 non-EOGIC with the aim of increasing sample-size in the control group, thus optimizing statistical analyses and ensuring study viability. Assuming a statistical power of 80% and a significance level of 5%, this sample size allows for the detection of statistically significant differences between the EOGIC and the non-EOGIC group in an exploratory approach. For continuous variables at a Cohen´s d of 0.385-medium size effect; and for categorical variables, with variables at a 10% prevalence in the non-EOGIC group, a15% of size-difference between groups; with variables at a 30–70% prevalence in the non-EOGIC group, a 20% difference between groups. Additionally, semi-supervised automatic learning will be employed for pan-tumor comparisons, a sample size of 60 EOGIC and 140 non-EOGIC patients is necessary to detect differences in an interest cluster of 20%.

This study is in agreement with international, national and local regulations for clinical studies (latest version of the Declaration of Helsinki, The Spanish Law for Biomedical Research and local regulations “Normas de Buena Práctica Clínica y Orden Foral 125/2009) as well as personal data protection (General Data Protection Regulation (RGPD-Regulation (EU) 2016/679), Spanish Organic Law 3/2018 and the local regulation “Resolution 1387–2017 of the Managing Director of the SNS-O”). Ethics Committee for Investigation with medicinal products from Navarra, have approved this project and a unified informed consent and patient-information sheet has been developed following guidelines of the Spanish Medication and Sanitary Product Agency (AEMPS). Previous to the inclusion, informed consent will be obtained for each patient.

### Data collection and analyses

Figure 2 shows a general outlook of the study. After signing the informed consent, patients will be registered and study data will be collected and managed using REDCap electronic data capture tools hosted at VHIO internal server [37, 38]. An automated ID will be generated for each patient. Demographic, clinical and histopathological data will be recorded; patient-reported questionnaires will be collected, and biological samples will be obtained for further analyses.

**Fig. 2 Fig2:**
[figure not shown]
General diagram of the study. Diagram summarizing patient recruitment criteria and data to be recorded in the TEOGIC study. EOGIC: early onset gastrointestinal cancer; ECOG: Eastern Cooperative Oncology Group

#### Demographic and clinical data and histopathological data

Recruiting medical personnel will be in charge of obtaining the variables in REDCap via a complete clinical interview and screening of the digital clinical record.

Demographic information related to the patients’ environment will be recorded, including, town of residence, country of origin and year of migration if applicable, housing status, social network, educational level and occupation.

In parallel, a comprehensive clinical profile of the patient will also be recorded, including ECOG Performance Status at diagnosis, height, current and usual body weight, body mass index, waist-hip ratio, allergy record, current medication, non-steroidal anti-inflammatory drug (NSAID) and antibiotics consumption, toxic habits, co-morbidities (*H. Pylori* infections and treatment, particularly for patients with GEC), previous surgeries in the affected organs, previously diagnosed malignancies and familial oncologic history as well as gynecological history for women. Additionally, a complete blood analysis covering a hemogram and a complete biochemistry as well as the tumoral markers carcinoembryonic antigen (CEA) and Carbohydrate antigen 19–9 (CA 19–9) will also be included.

#### Histopathological data and tissue proteome

General histopathological and molecular characteristics of the tumor will be comprehensively studied, via specific determinations relevant for each of the etiologies.

General histopathological characteristics, tumor location and clinical tumor stage will be recorded. Colorectal and gastroesophageal cancer staging will be assessed according to The Eighth Edition AJCC Cancer Staging Manual [39]. Pancreatic cancer will be classified as resectable, borderline resectable, locally advanced unresectable and metastasic. Number of metastasic sites and their location will also be recorded in stage IV of the disease. Histology type and differentiation grade will be assessed in formalin-fixed paraffin-embedded (FFPE) tissue. Molecular characteristics to be recorded in FFPE tissue include MMR/MSI status by immunohistochemical analysis of mismatch-repair proteins (*MLH1, MSH2, MSH6*, and *PMS2*) as well as CD3 and CD8 infiltration in all tumors. Additional molecular characteristics will also be measured according to tumor type: *HER2* amplification status, *KRAS*, *NRAS* and *BRAF* mutations for CRC; *HER2* overexpression/amplification status, PDL1 (CPS) and CLDN 18.2 and FGFR2b expression for GEC; and *KRAS* mutations for PC. For all tumors, Next-Generation Sequencing (NGS) analyses targeting cancer-related genes will be performed if a suitable sample is available.

Histopathological characteristics will be preferentially assessed in the recruitment center. If available after routine determinations for diagnosis and clinical management, FFPE tissue samples will be sent to the Pathology Department of HUN in order to perform a centralized assessment of missing determinations.

#### Lifestyle associated variables

Questionnaires related to dietary habits, physical activity and general quality of life will be collected for each patient.

*Dietary habits questionnaire*: a food-frequency questionnaire (FFQ) consisting on 136 items that evaluate intake of total calories, protein, carbohydrates, fats (saturated, mono and polyunsaturated), alcohol, cholesterol, fiber, vitamin A and vitamin C in the last year will be employed. This questionnaire was developed fully in Spanish and based on dietary habits in the country [40], since its development it has also been updated in agreement with food composition tables for Spain [41]. Due to its complexity it requires the assistance of trained personnel for its completion [40]. The questionnaire has been validated in several epidemiological studies, including studies in patients with cancer [41–44]. This questionnaire will always be answered with the assistance of trained personnel via telephone calls with the patient.

*Physical activity questionnaire*: the global physical activity questionnaire (GPAQ) developed by the World Health Organization consisting of 16 items that evaluate physical activity and sedentary behavior will be employed. This questionnaire has been extensively validated, also in patients with cancer [45, 46] and in its Spanish version [47]. Although initially developed for face-to-face interviews with trained personnel, several studies have validated administration of the questionnaire as self-reported [48–51].

*Quality of life questionnaire*: the short form health survey (SF-36) will be employed. The SF-36 questionnaire was developed in the USA to assess general health status in the Medical Outcomes Study [52]. Since then, it has been translated to numerous languages including Spanish [53, 54] and has been extensively validated in patients with cancer [55–57], within the Spanish context [58–60]. This questionnaire was initially developed to be self-reported [52], however, several studies have also reported its validity via telephone-calls or online [61–63].

In this study, the FFQ questionnaire will always be completed with the assistance of trained personnel via previously scheduled telephone calls with the patients. The GPAQ and SF-36 will be self-reported, and when needed, patients will be offered the assistance of trained personnel via telephone calls.

Of note, GPAQ and SF-36 questionnaires are designed to assess physical activity and quality of life at the time of questionnaire completion. Nevertheless, in this study, patients will be recruited after the diagnosis of cancer, which may heavily affect patients´ lifestyle. Moreover, it is the focus of this study to compare EOGIC and non-EGOIC patient´s general lifestyle and its impact on EOGIC development. Therefore, questionnaires will be adapted to evaluate patients´ lifestyle 1 year before diagnosis.

#### Circulating inflammatory protein profile

The circulating inflammatory protein profile will be obtained for each patient. For this purpose, blood samples will be obtained at the time of recruitment, and will always be treatment-naïve including surgery (i.e. samples will obtained before any kind of onco-specific therapeutic intervention, including resection intended surgery). A sample of 10 ml of total blood in vacutainer® EDTA tubes will be drawn by trained nurses. Thereafter, samples will be processed for plasma separation within 2 h since collection, following standardized work protocols in agreement with the Biobank of Navarrabiomed, and stored at -80ºC. Samples will be sent to Navarrabiomed-HUN for centralized storage and subsequent analyses.

In order to assess the circulating inflammatory profile of the patients, a panel of 96 key proteins involved in tumoral and inflammatory processes will be assessed (Olink® Target 96 Immuno-Oncology) by the proximity extension assay (PEA) technology.

#### Feces samples: microbiome analysis

Fecal microbiome analyses will be conducted by the sequencing the *16S* gene. Feces samples will be obtained at the time of recruitment, and will always be treatment-naïve including surgery. Samples will be self-collected by the patients following detailed instructions with the DANASTOOL Sample Collection MICROBIOME kit (Danagen). This kit consists of a sample collection instrument and a tube holding a stabilization solution that enables stabilization of DNA for several months at room temperature and indefinitely at -80ºC. Upon reception, feces samples will be homogenized and stored at -80ºC, thereafter they will be sent to Navarrabiomed-HUN for further processing and analyses.

DNA extraction will be conducted using the DANASTOOL Microbiome Fecal DNA kit (Danagen), and the quantity and quality of the extracted DNA will be assessed with NanoDrop ND-1000 (Thermo Fisher Scientific) and the Qubit Fluorometer (Thermo Fisher Scientific), and stored at -80ºC. For microbiome analyses, libraries will be prepared with the xGen Amplicon Panels for 16S and IST1 kit (IDT), which allows for the PCR-based enrichment on the *16S* v2 V1-V9 rRNA regions. Thereafter, sequencing will be carried out on the Illumina NovaSeqplatform. After quality control (QC) assessment, data will be processed with QIIME to obtain Operational Taxonomic Units (OTUs) against reference databases (Greengenes or Silva).

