#### Statistical analyses

Descriptive and comparative analyses will be performed separately for each type of tumor: CRC (Group A), GEC (Group B), and PC (Group C) as well as at a pan-tumor level, comparing all EOGIC to non-EOGIC patients.

Population characteristics will be described using measures of central tendency and dispersion for continuous variables and frequencies and percentages for categorical variables. Normality of the sample will be analyzed for continuous variables through histogram exploration, the Shapiro–Wilk test, and homoscedasticity by Levene's test. Group comparisons will be made using Student's t-test or Mann–Whitney U test for continuous variables and Pearson's Chi-square test or Fisher's exact test for categorical variables. Correlation between different measurements and conditions of interest will be assessed using Pearson's or Spearman's correlation tests.

Analyses for circulating inflammatory proteins, the microbiota and the tumor microenvironment proteome, will be conducted utilizing specialized software for each application. Raw data will be processed, applying quality criteria, and differential signatures between groups will be identified. For signature identification, previously mentioned tests, including correction methods for multiple comparisons such as the false discovery rate (FDR).

For pan-tumor and gender/sex-level comparisons, machine learning algorithms will be used, allowing integration of all patient clinical and lifestyle profile data with variables derived from circulating inflammatory proteins, microbiome and tumor microenvironment proteome profiles, identifying clusters of patients with similar patterns.

Statistical analysis will be performed using IBM Statistical Package for the Social Sciences (SPSS) version 24.0, GraphPad Prism v9, and R 4.1.0 (R Foundation for Statistical Computing, Vienna, Austria. http://www.R-project.org/).

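### Recent antibiotic use is neither ruled out at stool sampling nor used in the microbiota comparison, so unequal use between age groups could appear as an EOGIC signature

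*Protocol article*

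**What the plan says.** All references are to the protocol article.

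- **Sampling rule** (Feces samples: microbiome analysis): "Feces samples will be obtained at the time of recruitment, and will always be treatment-naïve including surgery". For blood, the section on circulating inflammatory proteins explains the same term: "samples will obtained before any kind of onco-specific therapeutic intervention, including resection intended surgery". So the term covers cancer treatment only.
- **Exclusion criteria:** performance status, comorbidities that hinder participation, and "Having received oncological treatment directed at the newly diagnosed cancer". Antibiotics are not mentioned.
- **Timing:** inclusion requires "Patients with newly diagnosed, histologically confirmed colorectal adenocarcinoma" (or the gastroesophageal or pancreatic equivalent), so stool is collected after the diagnostic work-up. No interval between work-up and sample is given.
- **What is known about the exposure:** the Background lists "alterations in the gut microbiota due to antibiotic consumption" among the factors associated with early-onset colorectal and gastroesophageal cancer.
- **What is recorded:** the clinical data include current medication and "non-steroidal anti-inflammatory drug (NSAID) and antibiotics consumption". No look-back window is stated. Bowel preparation is not mentioned anywhere.
- **What is analysed** (Statistical analyses): raw data are processed and "differential signatures between groups will be identified" with the general two-group tests listed there and false discovery rate correction. No adjustment, stratification or restriction is named.

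**The concern.** The article fixes when stool is taken and which prior exposure rules a sample out. That rule leaves out the exposure which the article itself says changes the measurement. A patient who had antibiotics during the presentation or work-up of the tumour can give stool that reflects the drug more than the disease or the age group. If this is more common in one age group, an unadjusted comparison reads it as a feature of that group.

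The article recognises the general problem elsewhere. Under Lifestyle associated variables it notes that "patients will be recruited after the diagnosis of cancer, which may heavily affect patients´ lifestyle" and moves the physical activity and quality-of-life questionnaires back to one year before diagnosis. Stool cannot be moved back in time, so its equivalent safeguard is to date recent exposures and use them in the analysis. The article states neither step.

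At stake is the biomarker aim. The Discussion names the microbiome as a source of non-invasive markers with potential for early diagnosis and screening. A marker of recent antibiotic treatment would not serve that purpose.

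**Working it through.** **Step 1. The plan's own detectable difference.** Inputs from Patient selection and recruitment: 80 EOGIC and 160 non-EOGIC, power 80%, significance level 5% (taken as two-sided), Cohen's d 0.385.

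EOGIC n = (1.960 + 0.842)² × (1 + 1/2) / 0.385² = 79.4, so 80. The figure reproduces and serves as a yardstick for the bias.

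**Step 2. Size of a spurious difference.** Suppose there is no true EOGIC effect, and recent exposure shifts a taxon or diversity index by D, in SDs of unexposed patients. With exposed proportions pE (EOGIC) and pN (non-EOGIC):

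- bias = D × (pE − pN)
- group variance = 1 + D² × p × (1 − p)
- SE = √(varE/n + varN/(2n)), with n the number of EOGIC patients
- rejection rate = that of a two-sided 5% z test with mean bias/SE

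The documents give no exposure rates or shifts. The values of pE, pN and D below are assumptions.

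| pE v pN | D | Bias (SD) | Rejection, 80 v 160 | Rejection, CRC 40 v 80 |
|---|---|---|---|---|
| 30% v 30% | 1 | 0 | 5% | 5% |
| 20% v 15% | 1 | 0.05 | 6% | 6% |
| 20% v 10% | 1 | 0.10 | 11% | 8% |
| 30% v 15% | 1.5 | 0.225 | 28% | 16% |
| 30% v 10% | 1.5 | 0.30 | 46% | 26% |

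Worked example, last row at 80 v 160: bias = 1.5 × 0.20 = 0.30; varE = 1 + 2.25 × 0.21 = 1.4725; varN = 1 + 2.25 × 0.09 = 1.2025; SE = √(1.4725/80 + 1.2025/160) = 0.161; bias/SE = 1.86; rejection 46%. If both group variances are set to 1, SE = √(1/80 + 1/160) = 0.137 and the range at 80 v 160 becomes about 6.5% to 59%.

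The largest bias in the table, 0.30 SD, is below the detectable 0.385. It takes more extreme assumptions to pass it: 50% v 20% with D = 1.5 gives 0.45 SD.

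**Step 3. Equal exposure.** At 30% in both groups and D = 1 the variance is 1 + 0.21 = 1.21, so the SE rises by √1.21 = 1.10. The detectable difference grows from 0.385 to 0.385 × 1.10 = 0.42 SD. This is a loss of precision without bias.

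**Step 4. False discovery rate control.** The rates above are for single tests at 5%. The correction makes the threshold stricter, but it deals with multiplicity. A taxon that differs because of unequal exposure does differ between the groups, so the correction does not remove the bias.

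**Step 5. Tumour mix.** The planned sizes are 40:80, 20:40 and 20:40, all 1:2. Colorectal cancer therefore makes up 40/80 = 50% of EOGIC and 80/160 = 50% of non-EOGIC patients. An exposure tied to colorectal cancer is balanced by design in the pan-tumour contrast if the targets are met.

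**The case against.** **Adjustment may sit in a fuller document.** Antibiotic use and current medication are collected, covariates are often left to a statistical analysis plan, and the patient instructions for the stool kit, which are not shown, might contain a waiting period. This stands in part: a missing covariate list would not be a finding by itself. But the article does state the sampling rule and the tests, and a later analysis plan can adjust for recent exposure only if the exposure was dated against the sample.

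**No differential exposure is shown.** This stands. The Background says that EOGIC usually presents at an advanced stage, which makes unequal antibiotic use plausible, but nothing in the article links stage to antibiotics. The direction could also be the reverse.

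**Bowel preparation.** A reader might infer that preparation for colonoscopy can also pass for an EOGIC microbiota. The article does not support that. It describes neither colonoscopy nor preparation, and gives no reason why preparation, or the time since it, should differ by age group within colorectal cancer. Tumour mix is balanced by the constant ratio (step 5). What remains is noise within colorectal cancer and a possible pull towards tumour-type clusters in the machine-learning step.

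**The aim for stool.** A reader might also infer that the study wants the long-term microbiota before disease, so that sampling after diagnosis defeats its purpose. The frame of one year before diagnosis is set for questionnaires only, and the antibiotic pathway is background, not an objective. The point rests on the biomarker aim.

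**The study is exploratory.** It is, and this limits the consequence of one false signal. It does not make a dated exposure less useful.

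**Conclusion.** The point holds in a conditional form. The plan rules out only prior cancer treatment before stool sampling and names no use of antibiotic data in the microbiota comparison, although it regards antibiotics as altering the microbiota. If recent use differs between the age groups, the planned tests can report it as an EOGIC signature. With assumed exposure of 20–30% against 10–15% and a shift of 1–1.5 SD, the bias is 0.05–0.30 SD, and the single-test false-positive rate is about 6–46% at 80 v 160 and 6–26% in colorectal cancer. These figures illustrate the mechanism and do not estimate what will happen in this study. With equal exposure the cost is precision only. For bowel preparation, no EOGIC bias is shown. The change is worth making because it is cheap and because exposure dates are harder to recover later.

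**What to change.** 1. Under Demographic and clinical data, add two REDCap fields: the date of the last antibiotic dose and the date of any bowel preparation, each to be read against the stool collection date. The clinical interview and record screening already planned can supply both.
2. Under Statistical analyses, prespecify that the microbiota comparison is adjusted for recent exposure (antibiotics in all groups, bowel preparation in colorectal cancer). Define the window for recent exposure before the data are examined. Keep earlier antibiotic use out of this adjustment, so that a long-term exposure is not adjusted away.
3. Add a sensitivity analysis restricted to patients unexposed within that window.

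The cost is two data fields and fewer samples in the sensitivity set, which matters most in gastroesophageal and pancreatic cancer (20 v 40 each). Sample size and sampling time stay as they are. Making the restricted set the main analysis, or collecting stool as late as possible before treatment, is not advised: the first could shrink these small groups selectively, and the second risks losing treatment-naïve samples.
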